## Abstract

**Background:**

Phenome-wide association studies (PheWAS) can reveal novel associations between variants in drug-target genes and disease and, as such, can be used to predict new drug-indication pairs for repurposing drugs with a known mechanism of action. A platelet-derived growth factor receptor beta (PDGFRβ) PheWAS demonstrated that patients with a single nucleotide variant that reduces PDGFRβ expression exhibit a higher prevalence of chronic skin ulcers, skin grafts, and reconstructive surgeries. Recombinant human platelet derived growth factor BB (rhPDGF) is a therapeutic that binds to and activates PDGFRβ and has received FDA approval for multiple indications, including improving healing of lower extremity diabetic neuropathic ulcers, augmenting periodontal bone and soft tissue reconstruction, and stimulating orthopedic bone regeneration. Leveraging a drug-repurposing methodology informed by PheWAS, we hypothesize that rhPDGF will provide therapeutic benefit in the treatment of other complex wounds, like full-thickness surgical wounds of the head or neck that cannot heal by primary intention following skin cancer excision.

**Methods:**

This prospective, double-blinded, single-site study aims to enroll 40 participants, randomized at a ratio of 1:1, comparing the efficacy of an advanced wound matrix saturated with rhPDGF or saline. Comparisons will be stratified by anatomical location (scalp/forehead versus face/neck) and maximum surgical defect dimensions (≤ 3cm versus > 3cm). The primary outcome of this study will evaluate the time in days to 81–100% granulation of the wound bed by expert clinical assessment of daily photographs. Secondary outcomes will assess the superiority of the rhPDGF-enhanced wound matrix relative to control with respect to wound granulation rate, epithelialization, complete wound healing, and patient reported outcomes (PROMs).

**Discussion:**

Although reconstructive techniques are available for healing complex head and neck wounds following skin cancer excision, these procedures are invasive, and older, frail patients are often suboptimal candidates. There remains a need for less invasive therapeutic approaches that reduce the healing time and mitigate the morbidity associated with chronic wounds. A PheWAS analysis identified complex wounds requiring reconstructive surgery as a novel drug-indication pair for repurposing rhPDGF. This protocol is designed to evaluate the efficacy of an rhPDGF-enhanced advanced wound matrix for healing complex head and neck wounds post skin cancer excision that cannot heal by primary intention.

**Clinical trial registration:**

This trial is registered at ClinicalTrials.gov (NCT06634030).

## Introduction

Phenome-wide association studies (PheWAS) are used to identify shared biological mechanisms across multiple diseases and conditions allowing for the identification of new drug indications and targets. These studies leverage electronic health record (EHR)-linked genetic data to identify associations between specific gene variants and aggregated diagnostic billing codes, or PheCodes. If FDA-approved drugs targeting a specific variant gene, protein, or pathway exist, PheWAS can predict novel drug-indication pairs, beyond the drug’s originally intended use. This is achieved by identifying phenotypes, derived from the PheCodes, that occur with a higher or lower prevalence among variant carriers compared to controls. These already approved drugs benefit from established safety data, are frequently available in cost-effective generic formulations, and offer significant advantages for accelerating development timelines through drug repurposing pathways.

Vanderbilt Health’s (VH) academic drug repurposing program leverages PheWAS to identify and validate associations between single nucleotide variants (SNVs) that result in specific protein alterations and disease phenotypes that may be amendable to targeted therapy (1–3). A PheWAS analysis of the platelet-derived growth receptor beta gene (*PDGFRB)* identified an association between SNV rs41287112, which decreases PDGFRβ expression, and an *increased* prevalence of chronic skin ulcers, skin grafts, and reconstructive surgeries in variant carriers. These findings suggest that targeting PDGFRβ may benefit treatment of complex wounds (4). Recombinant human PDGF-BB (rhPDGF) is a pharmaceutical therapeutic that binds and activates PDGFRβ, promoting chemotaxis, mitogenesis, and extracellular matrix deposition (5–7). It is FDA-approved for the treatment of lower extremity diabetic ulcers, periodontal bone and soft tissue reconstruction, and orthopedic bone regeneration with over 150 published clinical studies demonstrating its strong safety profile (8). Leveraging a PheWAS-driven drug repurposing strategy, we hypothesize rhPDGF therapy may be beneficial for non-diabetic, poorly-healing, complex wounds.

Skin cancer, including Basal Cell Carcinoma (BCC), Squamous Cell Carcinoma (SCC), and melanoma, is the most common cancer in the United States, affecting approximately one in five Americans during their lifetime (9–11). Skin cancer lesions are commonly found on the head and neck due to chronic ultraviolet (UV) radiation exposure and are commonly treated by Mohs micrograph surgery (for BCC and SCC) or wide local excision (for melanoma). These surgical approaches aim to achieve complete tumor excision while preserving healthy tissue and minimizing cosmetic deformities (12,13). In certain cases, full-thickness excision is required due to deep tumor invasion, and postoperative complications can be of concern depending on the tumor size, location, and depth, and the involvement of underlying structures such as muscle, fat, bone, or cartilage (14). Wound healing after surgery is particularly challenging when the margins cannot be approximated with staples, stitches, or glues and the defect is left to heal naturally by secondary intention. In retrospective studies of patients with complex surgical defects of the scalp and forehead with exposed bone, secondary intention healing took 13 to 26 weeks to fully re-epithelialize (15,16), increasing the chances of complications such as infection, necrosis, and unsightly scarring which are commonly associated with these complex wounds.

Rotational flaps and free flaps are reconstructive techniques where larger amounts of tissue with an intact blood supply are taken from a donor site on the patient and used to reconstruct a complex defect. However, older, frail patients are particularly vulnerable to complications and morbidity resulting from these invasive techniques and are often poor candidates for these surgical interventions. Recently, allografts, autographs, and xenografts made of extracellular matrix, cultured skin cells, or synthetic nanofibers have been reported as beneficial for the postoperative management of complex defects by providing protection against infection, promoting granulation and healing (17–21). These monotherapies that mimic individual components of the normal wound healing microenvironment show promise, but there is room for improvement with adjunct therapies that stimulate the signaling factors necessary for wound healing.

A PheWAS identified poorly-healing, complex wounds requiring reconstructive surgery as a novel drug-indication pair for repurposing rhPDGF. Reconstructive surgery for full-thickness surgical defects of the head and neck after skin cancer excision, which often result in exposed bone, is invasive and often challenging in the older population, resulting in increased risk of infection and necrosis. Non-invasive therapies that stimulate wound healing are an unmet need. We propose that rhPDGF will benefit healing of complex head and neck wounds by stimulating chemotaxis and mitogenesis of the cell types that deposit connective tissue, form new blood vessels, and regrow damaged tissue. This protocol will evaluate a rhPDGF-enhanced advanced wound matrix for complete healing of complex head and neck wounds that cannot heal by primary intention and have been referred for reconstructive surgery post skin cancer removal.

## Methods

### Trial design

This study will be carried out in accordance with International Conference on Harmonisation Good Clinical Practice (ICH GCP) and the United States (US) Code of Federal Regulations (CFR) applicable to clinical studies (45 CFR Part 46, 21 CFR Part 50, 21 CFR Part 56, 21 CFR Part 312, and/or 21 CFR Part 812). This Phase II clinical trial will compare the efficacy of an advanced wound matrix soaked in rhPDGF versus saline (control) to heal complex wounds of the head and neck whose margins cannot be approximated to heal by primary intention following skin cancer excision. This prospective, double-blinded, single-site study will randomize participants into two arms – intervention and control – comparing wound bed granulation, epithelialization, complete healing, and scarring and patient reported outcomes (PROMs), including pain and quality of life. The comparisons will also be stratified by anatomical location (scalp/forehead versus face/neck) and greatest dimension (≤ 3cm versus > 3cm) of the surgical defect. To achieve balance in treatment allocation, randomization blocks of 4 (2 interventions: 2 controls) for each stratification group will be employed.

After recruiting, consenting, and screening, eligible participants will undergo the baseline procedure to place the rhPDGF- or saline-saturated wound matrix into the wound bed. Following the baseline procedure, participants will return for their first follow-up visit on day 7 for removal of the foam bolster, clinical examination, photographs, and placement of standard wound dressing. Pain and adverse events will be evaluated and documented weekly through the participants’ electronic health records, phone calls, email surveys, or in-person visits. Participants will return for in-person study visits at weeks 4 and 8 for a clinical exam, photographs, and outcomes assessments and submit daily photographs of the wound while performing dressing changes at home starting on day 7 until day 56. The photographs will be taken using the NetHealth Tissue Analytics imaging application and automatically uploaded to the online platform. Blinded wound experts will analyze the photos, retrospectively, to determine the precise day that the wound bed achieved 81–100% granulation. The NetHealth Tissue Analytics imaging software will also be used to trace and measure granulation, epithelialization, and wound closure rates. Under routine care with a wound matrix (no rhPDGF), the average time to 81–100% granulation is 4–6 weeks in this patient population. Here, we aim to reduce the time to 81–100% granulation by adding rhPDGF.

The Standard Protocol Items: Recommendations for Interventional Trials (SPIRIT) schedule of enrollment, intervention, and assessments is included as Figure 1. A graphic study timeline of events is provided in Figure 2. The SPIRIT checklist is included in **S1 Appendix**. A full accounting of evaluations and unabridged protocol approved by the IRB is available in **S2 Appendix** (December 19, 2025; version 7.0) and important protocol modifications will be available from the corresponding author and by viewing the ClinicalTrials.gov (NCT06634030) study entry. A written sample consent form approved by the VH IRB is included in **S3 Appendix**.

### Setting

The trial will be conducted at Vanderbilt Health (VH) in Nashville, TN in the Department of Plastic Surgery.

### Recruitment and consent

This study aims to enroll 40 participants, 20 per arm, that are adults >21 years of age regardless of sex, race, or ethnicity. There is no information currently available regarding differential agent effects in participants defined by race or ethnicity. No vulnerable populations are expected to be enrolled in this study. The target number of patients to be recruited for enrollment is 200 with the expectation of consenting and randomizing ~25% of those and accounting for discontinuation, withdrawal, and loss to follow-up. This will be a single-site study at VH with an anticipated accrual rate of 1–2 participants per week.

Patients who have recently undergone Mohs surgery or wide local excision to remove skin cancer from the head or neck are referred to the PI for reconstructive surgery when the procedure leaves a complex surgical defect that cannot heal by primary intention. At the initial visit, patients that are determined to be eligible and interested in the trial will sign informed consent and undergo the baseline examination. Informed consent is initiated prior to the individual’s agreeing to participate in the study and continues throughout the individual’s study participation. Informed Consent Forms (ICF) are VH Institutional Review Board (IRB)-approved. Participants who signed consent but did not receive treatment will not be followed further.

### Participants

#### Inclusion criteria

Underwent surgery to remove skin cancer, either Mohs micrographic or wide local excision, that left a full-thickness surgical defect of the head or neck measuring between 1.5–10 cm in the greatest dimension with negative margins as determined by the Mohs surgeon or the pathology report following excision.Margins of the wound cannot be approximated or closed with stitches, sutures, staples, or glueSurgeon does not plan for immediate skin graft or flapAged >21 years oldWilling and able to provide informed consent and comply with the study protocolStated willingness to comply with all study procedures and availability for the duration of the study

#### Exclusion criteria

Clinically significant medical conditions that would, in the opinion of the investigator, compromise the safety of the participant with study participation and/or the ability of the participant to follow study protocolThe device will not fit the contour of the base of the wound bedHas evidence of current clinical infection as demonstrated by the invasion of bacteria into the healthy viable tissue on the periphery of the wound (colonization of wound bed due to normal flora or environment is not exclusionary)Prior radiation therapy at the application siteKnown allergic reactions to porcine tissue, porcine collagen, or yeast-derived productsCurrently enrolled in a drug or device trial or within 30 days of last investigational drug or device administration at baseline where investigational treatment (drug or device) was placed in wound bed or may potentially interact with study treatmentWomen who are known to be pregnant, breastfeeding, or planning to become pregnant during the trial

#### Screen failures

Screen failures are defined as participants who consent to participate in the clinical trial but are not subsequently randomized or for whom the wound matrix is unable to be placed in the wound bed. A minimal set of screen failure information is required to ensure transparent reporting of screen failure participants, to meet the Consolidated Standards of Reporting Trials (CONSORT) publishing requirements and to respond to queries from regulatory authorities. Minimal information includes demography, screen failure details, eligibility criteria, and any serious adverse events (SAE).

Individuals who consent and do not meet the criteria for participation in this trial (screen failure) because of the following criteria may be rescreened once the below criteria have been resolved.

Pathology report indicates margins aren’t yet clearHave an active infectionParticipation in an investigational study as outlined in exclusion criteriaPregnant or breastfeeding

### Randomization and blinding

Randomization will occur at the baseline visit at a ratio of 1:1 intervention to control. To achieve balance in treatment allocation, randomization blocks of 4 (1:1 intervention to control) will be stratified by anatomical location, scalp/forehead versus face/neck, and greatest dimension, </= 3cm versus > 3cm, of the surgical defect. Minor imbalance in treatment arm size may occur if there are incomplete randomization blocks. Blinding of the patients, investigators, and study team will be employed to reduce bias in conducting study activities and evaluations. The only personnel that will be unblinded will be an unblinded statistician and the scrub nurse that prepares the wound matrix, by soaking it in either rhPDGF or saline in the operating room. Once prepared, the wound matrix soaked in rhPDGF is indistinguishable from the wound matrix soaked in saline. In the case of a serious adverse event or medical emergency in which knowledge of the treatment is necessary for the participant’s well-being or medical care, the investigator will be unblinded to ensure appropriate medical management.

### Intervention

rhPDGF is highly purified, aseptically processed, and sterile filled into transparent glass syringes. One syringe contains a 0.5 mL solution of 0.3 mg/mL rhPDGF in 20 mM sodium acetate buffer pH6+/−0.5. The wound matrix is available in multiple sizes and can be trimmed or sutured together as needed. For one 4×2cm wound matrix, 4 mL, or 8 syringes, of rhPDGF (1.2 mg) will be used to saturate the matrix in a sterile dish, and multiple wound matrices may be used depending on the size of the wound. All components of the device are biocompatible and absorbable and will only be applied once.

### Administration

In this study the following process will be performed for administration of the intervention:

A clinical examination will be conducted to rule out infection, take photographs, and measure the size of the defect.The wound bed will be cleaned and debrided, as needed.The appropriate size wound matrix will be selected based on area of the wound.The matrix will be saturated with the appropriate volume of rhPDGF solution or saline in a sterile dish for at least 10 min.After the matrix is fully saturated, it will be placed into the wound bed and sutured at the margins.The matrix will be trimmed, as needed, to snug fit into the wound bed.The wound bed will be covered with foam bolster that does not get removed during the first week.

### Outcomes

#### Primary outcome

The primary outcome of this study will be to evaluate the potential efficacy of the rhPDGF-enhanced wound matrix on time (in days) to achieve 81–100% granulation of complex head or neck wounds following skin cancer excision. This will be assessed by expert clinical review and assignment of the percent granulation of the wounds in photographs taken daily starting at day 7.

#### Secondary outcomes

The secondary outcomes of this study will assess the effect of the rhPDGF-enhanced wound matrix on wound granulation, epithelialization, complete healing, and aesthetics and participant pain and quality of life after skin cancer excision. Wound granulation rate will be evaluated by percent granulation versus time and weekly ordinal scale outcomes of wound bed granulation (0–20% granulation = 1, 21–40% granulation = 2, 41–60% granulation = 3, 61–80% granulation = 4, 81–100% = 5) as determined by expert clinical review of photographs taken daily starting at day 7. Wound epithelialization will be evaluated by time (in days) to 100% epithelialization and percent epithelialization versus time, and complete healing will be evaluated by time (in days) to complete healing and wound size change over time. Epithelialization and complete healing will be measured utilizing the NetHealth Tissue Analytics software to trace and plot the change in the granulation tissue, new epithelial tissue, and the wound perimeter over time using the daily photographs of the wounds. An aesthetics survey and scar scale will be completed by expert clinicians based on visual assessment, final photograph, and final video completed during the Week 8 follow up visit. PROMs will evaluate change in pain and quality of life over the course of the 8 weeks on study.

#### Feasibility objectives

The feasibility objectives for this study will evaluate the feasibility of recruiting and retaining participants undergoing head and neck reconstruction after skin cancer excision. This will be measured by the total number of participants recruited and eligible, patients randomized per month, percent retention at end of study (8 weeks), and adherence to daily wound photograph schedule.

#### Safety objectives

The safety objectives for this study will evaluate rhPDGF treatment of complex head and neck wounds in patients who underwent skin cancer excision. This will be assessed by qualitative and descriptive summary of all adverse events associated with the intervention, such as but not limited to, wound size assessment, red skin rash around wound area, burning at the application site, swelling at the application site, bleeding at the application site, pain at application site, skin fibrosis around application site, and local recurrence rate of skin cancer.

### Study assessments and procedures

#### Safety assessments

Clinical examination
At the baseline visit and all follow-up study visits, clinical examination of the defect will visually assess for worsening of wounds including but not limited to infection, excess drainage, chronic inflammation, abnormal bleeding, or fibrosis.Patient medical history
At the baseline visit, patients meeting inclusion criteria will be screened for exclusion criteria through their medical history. Participants will review any known allergies, previous surgical procedures, previous complications, and frequency of BCC/SCC occurrence or recurrence.Pregnancy test
At the baseline visit, women of childbearing potential will be required to take a pregnancy test and must agree to use two reliable contraceptive methods for the duration of their participation in the study, one of which must be a barrier methodAssessment of adverse events
The following adverse events will be recorded in the eCRFs and followed until resolution:
Adverse events that are classified as related to study procedures (that is, potentially-, probably-, or definitely related to study procedures or of uncertain relationship to study procedures), regardless of severitySerious adverse events regardless of relatedness to study procedures.Clinical adverse events, events diagnosed as clinical conditions, with a severity grade ≥ 3, regardless of relatedness to study procedures.

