### Risks

The inclusion and exclusion criteria for this study were designed to minimize the risks to participants. The plethora of human safety data that is published supports the expectation that the only risk involved with the use of rhPDGF is the potential to increase acute inflammation at the site of application following intervention. The wound matrix is a biocompatible xenograft that is indicated for the management of wounds. It is contraindicated in individuals that have a known allergy to porcine tissue or active infection at the surgical site. The wound matrix should be used with caution in patients with impaired wound healing due to metabolic disorders, autoimmune diseases, or drug treatment. Potential adverse events that may be observed are those that may occur with any surgery including swelling, bleeding, hematoma, pain, and local inflammation or allergic reaction. The only other risks are associated with routine care procedures. Throughout the life cycle of the study, safety assessments will be used to ensure proper monitoring of adverse events. Safety assessments will consist of clinical examinations, evaluation of patients’ medical history, pregnancy testing, and weekly participant surveys. The potential benefits of this investigational drug and device to improve the healing rates and quality of life far outweigh the minimal risks in individuals with complex defects following skin cancer excision.

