##### Safety analyses

Monitoring and reporting of safety events will be conducted continuously as described in the Data and Safety Monitoring Plan. This section describes the assessment of safety endpoints at the time of final analysis. The frequencies of study-related adverse events and all other safety endpoints will be reported along with the treatment effect on the odds of these events (i.e., the odds ratio) and associated 95% confidence intervals using logistic regression for binary safety outcomes and the same methods for ordinal safety outcomes as those outlined for ordinal secondary endpoints above. Descriptive summaries of all adverse events will be provided.

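### Non-serious grade 1–2 adverse events judged unrelated to study procedures are not listed for recording, so the promised summary of all adverse events cannot be complete

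*Protocol article*

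**What the plan says.** The recording rule stands in the protocol article, Safety assessments, under Assessment of adverse events. Three classes are to be entered in the eCRF and followed:

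1. "Adverse events that are classified as related to study procedures", at any severity. The article spells out that this covers potential, probable and definite relationship, and also uncertain relationship.
2. Serious adverse events, whatever their relatedness.
3. Clinical adverse events "with a severity grade ≥ 3, regardless of relatedness to study procedures".

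Three other sections describe what will be collected or reported.

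- Safety analyses: "The frequencies of study-related adverse events and all other safety endpoints will be reported", with odds ratios and 95% confidence intervals. The section closes with "Descriptive summaries of all adverse events will be provided".
- Trial design: "Pain and adverse events will be evaluated and documented weekly", with no condition on grade or relatedness.
- Safety objectives: a "qualitative and descriptive summary of all adverse events associated with the intervention". The examples given are wound size, rash, burning, swelling, bleeding, pain, skin fibrosis and local recurrence of the cancer.

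**The concern.** The recording rule is narrower than the reporting promise. An analysis plan cannot repair this, because it cannot summarise events that were never entered.

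The gap also touches the safety objective. Most of the local events named there will be mild when they occur, and a mild non-serious event reaches the adverse-event record only through a judgement of relatedness. That judgement is made against study procedures, while the objective concerns the intervention. Every participant has recently had a cancer excision, which is a ready alternative cause outside the study procedures. The Risks section says "Potential adverse events that may be observed are those that may occur with any surgery" and includes local inflammation among them. Increased acute inflammation at the site is also the one risk that the same section expects from rhPDGF itself, so the expected product effect overlaps with events described as ordinary after surgery.

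In a randomised blinded trial, the comparison between arms is a better guide to causation than case-by-case attribution. Relatedness is therefore better held as a recorded attribute than used as a condition of entry.

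**Working it through.** The main check is one of logic; the article states no figure to reproduce.

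**Step 1. Cross the three recording rules.**

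| Event | Judged related, potentially related or uncertain | Judged unrelated |
|---|---|---|
| Serious, any grade | recorded | recorded |
| Non-serious clinical event, grade 3 or higher | recorded | recorded |
| Non-serious, grade 1–2 | recorded | **not listed** |

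Among grade 1–2 events there is one gap: those that are non-serious and positively called unrelated.

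**Step 2. Set the gap against each statement.**

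- Safety analyses, closing sentence (all adverse events): cannot be met in full.
- Safety analyses, study-related events: met, since these are recorded at any severity.
- Trial design, weekly documentation without restriction: wider than the eCRF list, and the two are not reconciled.
- Safety objectives, events associated with the intervention: not contradicted as worded, but exposed to misattribution.

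**Step 3. Ask which events named under Safety objectives depend on the adverse-event record.**

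- Pain: covered separately. Efficacy assessments has every participant complete the VAS at baseline and at all follow-up visits, in person or by phone.
- Wound size: covered by the software tracings.
- Bleeding and fibrosis: partly covered, because "clinical examination of the defect will visually assess for worsening of wounds" and both are among the signs listed. Trial design puts the in-person visits at day 7 and weeks 4 and 8, so an event that resolves between visits can be missed.
- Rash, burning and swelling: not named in the examination list, although that list is open-ended.
- Local recurrence: a non-serious, low-grade recurrence attributed to the original tumour meets none of the three rules, and the article gives no other recording rule for it.

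**Step 4. Illustrate the size.** The article gives neither event rates nor the share judged unrelated, so both are assumed here. Take 20 per arm, true local events in 8 v 4 participants, and the same share lost in each arm because the judgement is blinded. With a and c events of 20, the odds ratio is a(20 − c) / [c(20 − a)]. The Woolf 95% interval is exp(ln OR ± 1.96 × √[1/a + 1/(20 − a) + 1/c + 1/(20 − c)]).

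| Share lost | Recorded | Odds ratio | 95% CI | Rate, rhPDGF arm |
|---|---|---|---|---|
| 0% | 8 v 4 | (8×16)/(4×12) = 2.67 | 0.65–11.0 | 40% |
| 25% | 6 v 3 | (6×17)/(3×14) = 2.43 | 0.51–11.5 | 30% |
| 50% | 4 v 2 | (4×18)/(2×16) = 2.25 | 0.36–14.0 | 20% |

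The reported rate falls in proportion to the loss, the interval widens, and the odds ratio moves only modestly. The 50% row is an outer bound for illustration. It is not plausible for events at the application site when uncertain cases count as related.

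**The case against.** The strongest reply is that the rule is already generous. Potentially related and uncertain events are recorded at any grade, so an event is lost only if someone positively calls it unrelated. The study procedures include debriding the wound, suturing the matrix at its margins and leaving a bolster in place for a week (Administration). It would be hard to call swelling or bleeding at that spot definitely unrelated. The Risks section can also be read as listing these events among the hazards of taking part, which points toward recording them. Relatedness to procedures is in one respect broader than relatedness to the product. Odds ratios are promised for study-related events and other safety endpoints, not for every adverse event. Finally, limiting the capture of unrelated mild events is a legitimate choice, and the full protocol and the Data and Safety Monitoring Plan are not shown.

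Most of this stands, and it limits the size of the point. It does not remove the conflict, because the article states the recording rule expressly and then promises a summary wider than that rule. Weekly documentation may leave traces in health records or surveys, but the article gives no route from there to the analysis data for events outside the three classes. If the full protocol records more, this section of the article is what needs correcting.

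A reader might infer three stronger things that the documents do not support:

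- That low-grade events are recorded only if judged related. Serious events are recorded at any grade, and uncertain ones count as related.
- That the filter favours one arm. Randomization and blinding has patients, investigators and study team blinded.
- That Safety objectives is itself contradicted. Its wording is confined to events associated with the intervention.

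**Conclusion.** The point holds in a limited form. Non-serious grade 1–2 events positively classified as unrelated are not listed for the eCRF, which conflicts with the closing promise in Safety analyses and with the unrestricted weekly documentation in Trial design. The same gap can drop mild rash, burning, swelling, bleeding or fibrosis, or a low-grade non-serious recurrence, if these are attributed to the excision or the original tumour.

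The share lost is unknown and probably small; at zero the counts of these named events are unaffected. The consequence is under-counting in both arms and some loss of precision in the safety comparison. This rests on blinded attribution working alike in the two arms. The primary analysis, its power and its type I error are unaffected. The change is worth making because it is cheap and because mild events left unrecorded may not be recoverable later.

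**What to change.** 1. Under Assessment of adverse events, require every safety event named in Safety objectives to be recorded at the existing weekly contacts, whatever its grade and judged relatedness.
2. Keep relatedness as a recorded attribute, with separate entries for relatedness to the procedure and to the product.
3. Compare these events by arm, and note which participants were recorded under the present rule and which under the revised one. Because randomization is in blocks of 4 within strata, the change should fall on both arms about equally.
4. If other unrelated, non-serious, low-grade events are to stay unrecorded, reword the last sentence of Safety analyses to *all recorded adverse events as defined under Assessment of adverse events*, and align the weekly documentation statement in Trial design.

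The cost is a small change to the eCRF and the protocol wording, some extra data entry, and a change of recording rule in a trial that began enrolling in May 2025 and is due to stop in June 2026. Step 4 alone costs only wording. It would remove the contradiction but leave the relatedness filter on the named local events.
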